### 2.7. Statistical and analytical plan

The analytical strategy of the VOICE-DEP study is designed to support the primary and secondary objectives of the protocol while ensuring methodological transparency, reproducibility, and robustness. In accordance with the study design, the analysis will address three complementary dimensions: (i) descriptive characterization of the study sample and extracted variables, (ii) exploratory cross-sectional association and discrimination analyses between patients with depressive disorder and healthy controls, and (iii) longitudinal intra-individual modeling of changes in voice- and speech-derived variables in relation to clinical evolution.

First, a descriptive analysis will be performed for all study variables recorded in the case report form. Quantitative variables, including acoustic, paralinguistic, and linguistic features, will be summarized using means and standard deviations or medians and interquartile ranges, as appropriate according to their distribution. Qualitative variables will be described using absolute frequencies and percentages. This descriptive phase will include both baseline variables collected at V0 and longitudinal variables collected across repeated visits in patients. Age, sex, educational level and available socioeconomic-related variables will be compared between groups and considered as covariates in adjusted or sensitivity analyses when relevant imbalance is observed and the sample size permits stable estimation.

Second, the association between continuous voice- and speech-derived digital biomarkers and clinical severity measures will be explored using Pearson or Spearman correlation coefficients, depending on distributional assumptions. These analyses will focus on the relationship between multimodal voice-derived variables and clinician-rated depressive symptom severity measured with the MADRS, global clinical status measured with the CGI, and self-reported depressive symptom burden measured with the Patient Health Questionnaire-9 (PHQ-9).

For diagnostic discrimination between patients and healthy controls, classification models will be developed and evaluated. The area under the receiver operating characteristic curve (AUC) will be used as the principal performance metric, and additional measures such as odds ratios and their corresponding 95% confidence intervals will be reported where applicable. These analyses will be interpreted as exploratory because the study is a pilot methodological validation study rather than a definitive diagnostic accuracy trial.

Third, a systematic comparison between unimodal and multimodal approaches will be conducted. Unimodal models will include models based exclusively on audio-derived features or text-derived features, whereas multimodal models will combine acoustic, paralinguistic, and linguistic information. This comparison is intended to quantify the added value of multimodal integration beyond individual feature domains and is directly aligned with one of the predefined secondary objectives of the study.

Embedding-based acoustic features and contextual text embeddings will be evaluated exploratorily because previous studies suggest that they may capture clinically relevant patterns beyond predefined features [8,10,12,13]. Given their high dimensionality and limited interpretability, they will not constitute the primary analytical approach. Model specifications and extraction procedures will be fully documented to ensure transparency and reproducibility.

Longitudinal analyses will be used to evaluate the evolution of voice- and speech-derived digital biomarkers over time and their association with changes in depressive symptom severity and global clinical status. Because repeated assessments are obtained in the patient group at V0, V1, V2, V3, and V4, these analyses will account for within-subject correlation. Mixed-effects models and, where appropriate, finite-difference or change-score approaches will be used to examine intra-individual trajectories and their relationship with variation in MADRS, CGI, and PHQ-9 scores, as well as with relevant treatment-related variables. Treatment exposure and changes during follow-up will be included, where feasible, as time-varying covariates in the mixed-effects models. Treatment-specific analyses will be considered exploratory and will not be interpreted causally.

Psychotic status will be considered as a potential confounder and included as a binary covariate when the sample permits stable estimation. Sensitivity analyses excluding patients with psychotic depression will be performed, while subgroup comparisons will be considered exploratory.

Regularized logistic regression will be the primary classification model, with a linear support vector machine and random forest models used for comparison. Missing data, including their frequency, pattern, and documented reasons, will be reported by variable and visit. Mixed-effects models will include a participant-specific random intercept, time as a fixed effect, and selected time-varying covariates; a random slope for time will be considered if supported by the data. The Benjamini–Hochberg procedure will control the false discovery rate within each feature family, and feature selection and hyperparameter tuning will be performed within each training partition.

Because repeated recordings from the same patient are not independent, all longitudinal analyses, predictive modeling and validation procedures will use participant-level data splitting and account for within subject correlation, in order to preserve the independence of training and test data. Specifically, all recordings from the same participant will be assigned exclusively to either the training or the test partition, in order to reduce optimistic bias due to repeated observations from the same individual and avoid information leakage. In this context, Leave-One-Group-Out cross-validation will be used as an appropriate validation framework for grouped repeated-measures data.

To improve clinical interpretability, feature attribution analyses will be performed using Shapley-based methods, including SHAP values where applicable. These analyses will help identify which acoustic, paralinguistic, and linguistic signals contribute most strongly to model predictions and will support the interpretation of the relative importance of different multimodal domains. No imputation for missing data will be applied. To maximize the data collection, quality control reviews will be conducted after every visit. A flexible time-window for visits and periodic reminder phone calls will be planned to reduce the risk of follow-up losses.

All analyses will be performed using Python v3.x or equivalent validated statistical software. Statistical significance will be considered at a two-sided threshold of p < 0.05.

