### 2.4. Sample size and sampling strategy

The planned study sample comprises 75 participants: 25 patients with a clinical diagnosis of moderate or severe unipolar depression and 50 healthy controls. Patients will be assessed at five time points: baseline (V0) and four monthly follow-up visits at 30, 60, 90 and 120 days, each with an allowed window of ±7 days. Assuming complete follow-up, this will generate 125 longitudinal voice recordings in the clinical group. Healthy controls will undergo a single baseline assessment, generating 50 voice recordings. The planned dataset therefore comprises 175 voice recordings.

The sample size was defined pragmatically as a feasible recruitment target for a hospital-based feasibility and methodological pilot study conducted in a real-world clinical setting. The study is not intended as a definitive diagnostic accuracy trial powered to estimate the performance of a final clinical classifier. Rather, it is designed to evaluate the feasibility, standardization, reproducibility and analytical validity of a multimodal voice- and speech-based methodology for depression assessment and longitudinal monitoring.

As a quantitative sensitivity analysis, a baseline comparison of 25 patients and 50 healthy controls, with a two-sided significance level of 0.05 and 80% power, would detect a standardized mean difference of approximately Cohen’s d = 0.70. The study is therefore primarily sensitive to moderate-to-large effects. This is presented as a sensitivity analysis because reliable prospective effect-size estimates are not available for the multiple exploratory speech-derived variables included.

The sampling strategy will be consecutive and non-probabilistic. Eligible patients will be recruited during routine clinical care in the Department of Psychiatry, including both outpatient consultations and inpatient care. Healthy controls will be invited by members of the research team and assessed after confirmation of eligibility.

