Although a balanced baseline comparison between patients and healthy controls would be methodologically desirable, the final allocation was defined according to feasibility considerations. Healthy controls will be individually matched to patients by age and sex whenever feasible. If individual matching cannot be achieved, control recruitment will be guided by the age and sex distribution of the patient group to obtain group-level frequency matching as closely as possible. Recruitment of clinically characterized patients with moderate or severe depressive disorder is expected to be more demanding because it requires repeated clinical assessments and longitudinal follow-up. In contrast, healthy controls require only a single baseline visit, allowing the inclusion of a larger control group without substantially increasing study burden. Therefore, the study will include 25 patients and 50 healthy controls. This design is expected to strengthen the baseline characterization of non-depressed speech patterns while preserving the longitudinal focus of the clinical cohort.

At participant level, baseline analyses will compare patients and healthy controls, whereas longitudinal analyses will focus on within-patient changes across repeated assessments. For predictive modeling, the imbalance between groups will be explicitly considered through appropriate analytical strategies, such as participant-level data splitting, balanced resampling, class weighting or sensitivity analyses when applicable.

Given the pilot nature of the study and the moderate sample size, classifier performance estimates will be interpreted as exploratory and hypothesis-generating. The study will prioritize transparent feature extraction, reproducible preprocessing, clinically interpretable modeling and longitudinal within-subject analysis over the development of a definitive deployable diagnostic model. Model complexity will be limited in relation to the available sample size, and classifier performance estimates will be accompanied by confidence intervals whenever feasible.

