**Table 2 pone.0353827.t002:** Study variables recorded in the VOICE-DEP case report form and assessment schedule.

Domain	Description	Assessment visits
Participant identification	Participant category (patient or control), study code, and visit date	V0–V4 in patients; V0 in controls
Sociodemographic and anthropometric baseline variables	Sex, age, marital status, place of residence, birth order in the sibship, height, weight, body mass index, body surface area, educational level, childcare responsibilities, caregiving responsibilities for dependent relatives, religious belief, community religious practice, and social relationships	V0 only
Lifestyle, family history and contextual baseline variables	First-degree family psychiatric history, toxic habits, tobacco, alcohol, cannabis, cocaine, amphetamine and other substance use, physical activity, diet pattern, complementary or alternative treatments and specific prescribed diets, pharmacogenetic or pharmacodynamic isoform information when available, employment status, night work, acute and chronic stressful life events, and current and lifetime traumatic events	V0 only
Clinical baseline variables	Principal diagnosis according to ICD-10 depressive categories, psychiatric comorbidities, medical comorbidities, previous suicidal ideation, previous suicidal behavior, previous self-harm, duration of the current episode, time since initial diagnosis, and number of previous depressive episodes	V0 only
Recording and audio traceability variables	Whether the voice recording was obtained, pseudonymized audio file identifier, presence of recording incidents, and type of incident (patient need, clinical need, technical problem, others)	V0–V4 in patients; V0 in controls
Clinician-rated and self-reported symptom variables	Depressive symptom severity assessed with MADRS, global clinical impression assessed with CGI, and self-reported depressive symptom burden assessed with PHQ-9	V0–V4 in patients; V0 in controls
Pharmacological treatment variables	Pharmacological treatment received, including total daily dose in mg/24h, dosing interval, administration time, and duration of treatment at the recorded dose	V0–V4 in patients
Non-pharmacological treatment and psy-chotherapy variables	Sleep hygiene measures, diet pattern, regular physical activity, discontinuation of toxic habits, psychotherapy attendance, psychotherapy type, and psychotherapy frequency	V0–V4 in patients

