Neurostimulation variables	Receipt of electroconvulsive therapy in the current episode, type of electroconvulsive therapy, and other neurostimulation treatments	V0–V4 in patients

**Table 3 pone.0353827.t003:** Multimodal voice- and speech-derived variables predefined in the VOICE-DEP protocol.

Domain	Variable/ group of variables	Operationalization/ measurement
Acoustic	Pitch	F0 mean, standard deviation and range (Hz).
	Energy/ intensity	Mean and standard deviation (dB).
	MFCCs	Coefficients 1–13 summarized by mean and standard deviation.
	Harmonic-to-noise ratio	dB.
	Jitter	Percentage (%).
	Shimmer	Percentage (%).
	Spectral descriptors	Spectral centroid, roll-off and slope (Hz or normalized units).
	Formants	F1–F3 mean frequency and bandwidth (Hz).
	Spectral/ prosodic entropy	Dimensionless entropy index.
	Embedding-based acoustic features	High-dimensional vector representations derived from pretrained models (e.g., Wav2Vec2, HuBERT).
Paralinguistic	Speech rate/ articulation rate/ pause duration	Words per second and pause duration in seconds.
	Prosodic range	F0 and intensity variability (Hz, dB, or coefficient of variation).
	Pause ratio	Silence-to-speech proportion (0–1 or %).
Linguistic	Sentiment polarity	Continuous score from −1 to +1.
	Negative emotional word ratio	Percentage (%) of negatively valenced words.
	First-person singular pronouns	Percentage (%) or frequency per 100 words.
	Lexical diversity	MTLD, Honor´e and type-token ratio.
	Word count/ mean sentence length	Number of words and words per sentence.
	Lexical sentiment variance	Standard deviation of sentiment scores.
	Lexical coherence/ cohesion	Cosine similarity based on semantic embeddings.
	Contextual text embeddings	High-dimensional representations extracted from a pretrained open-weight language model.

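### Tobacco use is recorded at baseline but is neither matched on nor named for adjustment, so any smoking difference between groups would pass into the unadjusted acoustic contrast

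*Protocol article*

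**What the plan says.** Section 2.4 states: "Healthy controls will be individually matched to patients by age and sex whenever feasible". If that fails, the fallback is frequency matching on the same two variables.

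Section 2.7 then lists what is compared between groups and may enter as a covariate: "Age, sex, educational level and available socioeconomic-related variables will be compared between groups and considered as covariates in adjusted or sensitivity analyses". This applies only when a relevant imbalance is seen and the sample allows stable estimation. The only other variable that section 2.7 calls a potential confounder is psychotic status: "Psychotic status will be considered as a potential confounder and included as a binary covariate when the sample permits stable estimation". Psychotic status cannot vary among controls. Treatment exposure enters only the within-patient mixed models.

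Table 2 (section 2.6) records "toxic habits, tobacco, alcohol, cannabis, cocaine, amphetamine and other substance use" at V0, in the lifestyle domain and apart from the sociodemographic row. Section 2.7 promises a descriptive summary of every case report form variable, which includes tobacco, but gives it no other role. Section 2.2 excludes only intoxication at assessment, so smokers are eligible in both groups.

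Table 3 predefines F0, jitter, shimmer and "Harmonic-to-noise ratio" as acoustic variables. They belong to the primary outcome variables of section 2.6 and to the contrast named in the primary objective.

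**The concern.** A healthy control group supports a statement about depression only to the extent that the groups are alike in other things that shape the voice. Smoking is a plausible such factor for features generated at the larynx. It is already measured, yet the plan neither balances it nor adjusts for it. The phrase about socioeconomic variables does not naturally cover it, because Table 2 files tobacco under lifestyle.

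If the groups differ in smoking, a feature unrelated to depression could separate them, or a real difference could be masked, depending on direction. The Shapley-based attribution in section 2.7 could then credit depression with a signal that belongs to smoking. Participant-level splitting, cross-validation and Benjamini–Hochberg control do not remove confounding.

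**Working it through.** **Inputs from the protocol (section 2.4).** "25 patients with a clinical diagnosis of moderate or severe unipolar depression and 50 healthy controls"; "with a two-sided significance level of 0.05 and 80% power"; "would detect a standardized mean difference of approximately Cohen’s d = 0.70".

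**Inputs assumed.** The documents give neither smoking prevalence by group nor the effect of smoking on any voice feature. Assumed: a prevalence gap of 10–40 points and an effect of 0.3–1.0 SD on an affected feature.

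**1. The plan's own figure.** The normal approximation gives (1.960 + 0.842) × √(1/25 + 1/50) = 0.686. The noncentral t with 73 degrees of freedom gives 0.695, and power at d = 0.70 is 80.5%. The stated 0.70 reproduces.

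**2. Bias with no depression effect.** Bias = (smoking share in patients − share in controls) × effect of smoking.
- Low end: 0.10 × 0.3 = 0.03 SD.
- Middle: 0.25 × 0.8 = 0.20 SD.
- High end: 0.40 × 1.0 = 0.40 SD.
- Equal shares: 0.

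**3. Per-feature false-positive rate.** Two-sided 0.05 t-test, 25 vs 50, noncentrality d × √(25 × 50/75), before any false-discovery control:

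| Bias (SD) | Rejection rate |
|---|---|
| 0.03 | 5.2% |
| 0.06 | 5.7% |
| 0.20 | 12.7% |
| 0.40 | 36.4% |

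The table treats the bias as a fraction of the total SD. If the effect is stated in SDs within smoking strata, smoking also widens the spread and the top figure falls: at 50% vs 10% smokers and 1.0 SD, d is 0.37 and the rate about 31%.

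**4. Masking.** If a bias of 0.20 SD opposes a true d of 0.70, the visible difference is 0.50 and power falls from 80.5% to 52.2%. With a bias of 0.06 it is 73.2%.

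**5. On the AUC scale**, the plan's principal metric. For a single feature with no depression effect, AUC = Φ(d/√2). From 30% vs 20% smokers with 0.3 SD up to 50% vs 10% with 0.8 SD (within-stratum), d is 0.03–0.31 and AUC 0.51–0.59 instead of 0.50.

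**6. Effect of adjusting when the feature is the outcome.** In a simulation with 40% vs 20% smokers, 0.8 SD and no depression effect, adding smoking as a covariate moved the mean group difference from 0.16 SD to 0.00 and the rejection rate from 9.4% to 5.1%.

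**7. Effect of adding tobacco to the classifier.** At 45% vs 20% smokers and 0.8 SD, a feature with no depression effect has an AUC of about 0.55. Tobacco alone has an AUC of 0.5 + (0.45 − 0.20)/2 = 0.625. Adding it as a predictor therefore raises the model's AUC to about 0.62, although the voice feature carries nothing about depression.

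**8. Can an imbalance test decide?** A test of the smoking shares at 25 vs 50 has power of about 17% for 30% vs 20% and 46% for 40% vs 20%. Even with an equal population prevalence of 20–30%, a gap of at least 10 points arises by chance in about 36–42% of samples.

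**The case against.** The strongest reply is that both links in the chain come from outside the documents. Nothing in the protocol says that tobacco alters these features or that patients smoke more. This stands, and it is why the point is conditional and the size is given as a range.

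A reader might infer that unequal smoking is built into the design, since controls with any psychiatric history are excluded and patients with comorbidity are not. Section 2.2 does not support that: it does not say that tobacco use counts as a psychiatric disorder, and ordinary smokers may enter either group.

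The t-test rates are not the plan's operating error rates. The headline metric is AUC from regularized logistic regression, and feature tests are subject to Benjamini–Hochberg within family. This also stands; the rates are illustrations per feature.

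It can further be said that the descriptive tables would reveal an imbalance, that socioeconomic adjustment may remove part of it, that the list need not be exhaustive, that a separate analysis plan may add tobacco, and that the results are labelled exploratory. These points lower the stakes. They do not change the fact that the protocol names a specific list and tobacco is not on it, and calling an estimate exploratory does not remove bias from it.

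Finally, alcohol, body mass index and medical comorbidities are not named either. That is so. The case for tobacco rests on its plausible direct route to the laryngeal features.

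**Conclusion.** The point holds in conditional form. As written, the plan gives a recorded baseline variable no part in matching, group comparison or adjustment, while features that it may plausibly affect enter the patient–control contrast. Under the assumed ranges the bias is about 0.03–0.40 SD per affected acoustic feature, with a false-positive rate before false-discovery control of about 5–36%. All of it lies below the 0.70 SD that the study is sized to detect.

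A reader might infer that smoking will be read as depression across the whole contrast. The documents do not support this: the expected bias is zero if smoking shares are equal, only some acoustic features are in question, and no case is made for the linguistic ones. The change is worth making because it is cheap, not because the bias is established.

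**What to change.** In the covariate sentence of section 2.7:

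- Add V0 tobacco use (current vs not) to the variables compared between groups.
- Include it as a covariate in the V0 patient–control comparisons where the acoustic feature is the outcome. Do not make this depend on a significance test of imbalance, given the low power shown above.
- For the classifier, do not add tobacco as a predictor. Repeat the AUC and the feature attribution in current non-smokers as a sensitivity analysis, reported as exploratory.

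**Cost.** No new data are needed. Adjustment inflates the variance of the group contrast by 1/(1 − R²), where R² is that of group on smoking. For 30%, 40% and 50% vs 20% smokers this is 1.013, 1.048 and 1.105, which moves the detectable d from 0.695 to 0.70, 0.71 and 0.73. At 50% vs 10% it is 1.248 and 0.78. The non-smoker analysis is smaller: with 40% vs 20% smokers it keeps 25 × 0.6 = 15 patients and 50 × 0.8 = 40 controls. The detectable d by the normal approximation is then 2.802 × √(1/15 + 1/40) = 0.85, so it can show instability but not settle the question.

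### Age and sex are modelled only if imbalance is seen, although controls are matched on both; unadjusted baseline comparisons of strongly sex-dependent features are then conservative and lose power

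*Protocol article*

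**What the plan says.** Three statements in the protocol article bear on this point.

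- **Matching (section 2.4).** "Healthy controls will be individually matched to patients by age and sex whenever feasible". If that fails, control recruitment follows the patients' age and sex distribution "to obtain group-level frequency matching as closely as possible".
- **Covariates (section 2.7).** Age, sex, education and socioeconomic variables are compared between groups and then "considered as covariates in adjusted or sensitivity analyses when relevant imbalance is observed and the sample size permits stable estimation". One rule covers all of them, and the matching factors get no separate treatment.
- **Feature scale (section 2.6, Table 3).** Pitch is defined as "F0 mean, standard deviation and range (Hz") and formants as "F1–F3 mean frequency and bandwidth (Hz"). Only prosodic range has a coefficient-of-variation option. Section 3.2 places scaling inside the training partitions and does not describe it as sex-specific.

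No other statement brings age or sex into the baseline comparison, the severity correlations or the classifier, and no matched analysis is stated.

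**The concern.** The trigger for adjustment is the very thing that matching is meant to prevent. If matching succeeds, no relevant imbalance is seen and the rule does not fire.

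Bias from imbalance is only one reason to model a matching factor. The other is precision. When a feature differs between men and women, that difference adds to its variance in both groups. Matching makes the group difference itself more stable, but an unadjusted test still computes its standard error from the full variance. The standard error is then too large and the test too cautious.

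The rule also lets the observed data choose the model, which sits poorly with the aim of a reproducible analytical framework. Patient-control discrimination is part of the primary objective (section 2.1). A pilot that screens candidate markers could therefore set aside a sex-dependent feature as uninformative when only the analysis made it look so.

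**Working it through.** **Inputs from the document (section 2.4).** The sensitivity analysis is for "a baseline comparison of 25 patients and 50 healthy controls", "with a two-sided significance level of 0.05 and 80% power", and states that this "would detect a standardized mean difference of approximately Cohen’s d = 0.70".

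**Inputs that are assumptions.** The document does not say how strongly any feature depends on sex. Let D be the male-female gap in within-sex SDs, varied from 0 to 4. Let p be the share of women: 48% (12 of 25 patients, 24 of 50 controls) or 68% (17 of 25, 34 of 50). Sex is exactly balanced between the groups.

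**Step 1: the plan's own figure.** Detectable difference = (1.96 + 0.84) × √(1/25 + 1/50) = 2.80 × 0.245 = 0.686. The noncentral t with 73 degrees of freedom gives 0.695. The stated 0.70 is reproduced. It refers to the total SD in an unadjusted comparison.

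**Step 2: what a sex gap does to the total SD.** Inflation factor k = √(1 + p(1 − p)D²). At p = 0.48 and D = 2: √(1 + 0.2496 × 4) = 1.41. A difference of 0.70 within-sex SD is then only 0.70/1.41 = 0.50 total SD.

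**Step 3: power under exact balance.** The group difference has true standard error √0.06 = 0.245 within-sex SD, because balance cancels the sex component. The unadjusted test uses about 0.245 × k. Approximately:

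- power = Φ(0.70/0.245 − 1.96k)
- detectable effect at 80% power = (1.96k + 0.84) × 0.245

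At D = 2 the first formula gives Φ(2.86 − 2.77) = 53%; simulation of the t-test gives 51%. Power and type I error below are simulated (20,000 runs per scenario, p = 0.48, true effect 0.70 within-sex SD). The detectable effect is from the formula.

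| D | k | 0.70 in total SDs | Power, unadjusted | Power, sex in model | Type I error, unadjusted | Detectable within-sex effect, unadjusted |
|---|---|---|---|---|---|---|
| 0 | 1.00 | 0.70 | 80% | 80% | 5.2% | 0.69 |
| 1 | 1.12 | 0.63 | 73% | 80% | 2.7% | 0.74 |
| 2 | 1.41 | 0.50 | 51% | 80% | 0.6% | 0.88 |
| 3 | 1.80 | 0.39 | 23% | 80% | below 0.1% | 1.07 |
| 4 | 2.23 | 0.31 | 5% | 80% | below 0.1% | 1.28 |

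With 68% women, unadjusted power at D = 1, 2, 3 and 4 is about 74%, 55%, 28% and 8%. With sex in the model, type I error stays near 5% throughout. Unadjusted power falls to 40%, half of the planned 80%, at D of about 2.5.

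**Step 4: single-feature AUC (50% women, effect 0.70 within-sex SD).** Pooling the sexes gives

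AUC = 0.5 Φ(0.70/√2) + 0.25 Φ((0.70 + D)/√2) + 0.25 Φ((0.70 − D)/√2).

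This is 0.69 at D = 0, then 0.67, 0.63, 0.61 and 0.60 at D = 1, 2, 3 and 4. Within sex it is 0.69 throughout.

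**The case against.** Several points on the other side are sound.

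- **The size rests on a figure the document does not give.** A reader might infer that most of the sensitivity on pitch and formants is lost. That needs a gap of about 2.5 within-sex SDs or more. At a gap of 1 the loss is modest (73% against 80%). Mean F0 may have a large gap, but that is an assumption. For formants and for age there is no figure at all, so the strong statement should not be made for them.
- **Scope is limited.** Much of Table 3 (pauses, speech rate, pronouns, sentiment, lexical diversity) has no demonstrated sex gap of this size. The longitudinal models carry a participant random intercept, which absorbs stable differences in level.
- **The principal metric is classifier AUC, not a t-test.** A multivariable classifier can recover some of the sex information from other features. In a population calculation, adding two features with a gap of 2 raised AUC from 0.61 to 0.65 when the main feature's gap was 3, and from 0.60 to 0.63 when it was 4. Within sex the single feature reaches 0.69, so recovery is partial.
- **Imperfect matching is the case the rule addresses.** A reader might infer that the classifier will learn sex or age instead of depression. If matching fails visibly, the rule calls for adjustment to be considered, so this does not follow from the text.
- **The study is an exploratory pilot, and the error is on the cautious side.** Under good matching the harm is missed signals, not false claims.
- **Details may sit in a fuller plan.** This carries less weight, because the article does not stay silent: it states a rule, and the trigger of that rule is the problem.

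These points narrow the claim and lower its weight. None of them repairs the rule for the cross-sectional analyses.

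**Conclusion.** The point holds in a limited form. Tying adjustment for age and sex to observed imbalance, after matching on both, tends to leave the matching factors out when matching works. For strongly sex-dependent features on a raw Hz scale, the unadjusted baseline comparison is then conservative and loses power. The loss runs from slight (gap of 1) to nearly complete (gap of 4).

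These figures assume exact balance on sex, equal within-sex variance, normal data and a true effect of 0.70 within-sex SD. They ignore the false-discovery-rate control also planned in section 2.7. Group comparisons bear the full loss; severity correlations and classifier AUC bear part of it. Within-patient mixed models and features weakly related to sex are largely unaffected. No age effect has been quantified.

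This is a moderate point and a nearly free improvement, not a flaw that undermines the study.

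**What to change.** In section 2.7, state that age and sex enter the baseline analyses by default, whatever imbalance is observed:

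- **Feature comparisons:** feature ~ group + sex + age.
- **Classifiers:** account for both factors, for example by covariate adjustment or sex-specific standardisation, fitted within the training folds only.
- **Other covariates:** keep the imbalance rule for education and socioeconomic variables.

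It would also help to say in section 2.4 that d = 0.70 is in total-SD units of an unadjusted comparison. Expressing F0 in semitones and keeping matched sets in the same fold are optional.

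The cost is one sentence in section 2.7 and two degrees of freedom out of 73. Both variables are already in the case report form. Section 2.10 puts the analysis in February 2028 with recruitment still under way, so the change can still be fixed before the data are examined.
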